**Registration number::**

ChiCTR1800019463

## Introduction

1

Peripheral facial paralysis (PFP) is a common peripheral neural disease. The prevalence of PFP among urban residents in China is 425.7 per 100,000 population, and 258 per 100,000 individuals in rural areas, which are significantly higher than the annual incidence of 20 per 100,000 people in European and American countries, and the incidence of PFP is still increasing.^[1,2]^ Facial damage is the major clinical symptoms for PFP patients, which disfigures the appearance and have a great impact on patients’ social interaction, work and life, causing a heavy psychological burden or even derailing sufferers from society.

It is known that acupuncture treatment combined with facial paralysis (FP) rehabilitation guided by doctors is a routine method of PFP treatment in China; however, there are always 2 problems.^[3,4]^ On one hand, the acupuncture effect cannot be displayed validly in real time and it lacks convincing power in the clinical research of PFP because of the unclear acupuncture treatment mechanism, the scarcity of objective, and dynamic evaluation indicators. On the other hand, rehabilitation training has always been depended on the doctor's verbal guidance to the patient, but not the intuitive and interactive methods, so the effect of patient's FP rehabilitation training is limited after returning home.

At present, the clinical evaluations of facial nerve function after FP are mainly based on scales, of which House-Brakmann (H-B) rating scale is the most widely used. Although H-B rating scale has no specific and clear quantitative indicators to describe the severity of facial nerve injury, resulting in deficiencies in utility and reliability.^[4,5]^ In addition, the objective diagnostic indexes of PFP are neuroelectrophysiological diagnostic tests including surface electromyogram (EGM), nerve excitability measurement, facial nerve electrogram, EGM (the criterion standard for judging the prognosis and efficacy of facial nerves), blink reflex (BR, the most sensitive index for early diagnosis of FP to directly or indirectly reflect facial nerve conduction function) and F wave. Unfortunately, in clinical practice, EGM alone cannot reflect the degree of inhibition, damage and degeneration of the electrical conduction of the nerve, especially the low positive rate of detecting mild-to-moderate FP, besides, the facial nerve function cannot be evaluated in the acute stage of the lesion, making the detection lagging. BR requires professional operation, and the process is complicated, causing pain and discomfort to the patient, resulting in poor patient acceptance.^[6]^ Electrophysiological testing cannot dynamically reflect the evolution of FP but only shows the facial nerve function currently being examined. It is difficult to provide effective objective assessment of acupuncture for FP.

Facial nerve compression of FP is mainly caused by local neurotrophic vasospasm and tissue edema due to inflammation, edema, ischemia, or autonomic nervous system disorder in the facial neural canal and surrounding tissues.^[7]^ Some in-depth researches believed that facial nerve ischemia in patients with FP can lead to different degrees of blood circulation disorders, and its recovery depends on stable internal neurological environment and nutritional supply, which are based on good blood circulation.^[8,9]^ A comprehensive understanding of the blood circulation of the facial nerve can help evaluate the development and prognosis of PFP; thus, a new method for evaluating FP was proposed based on the dynamic observation of local conditions of PFP using infrared thermal imaging.^[10,11]^ Nevertheless, infrared thermal imaging has high environmental requirements, blurred imaging, poor experimental consistency, and insurmountable technical defects.^[12]^

In clinic, individualized acupuncture treatment programs are provided for FP patients according to the severity of FP, the development and change of the condition, different physical conditions, and syndromes. It is urgent to comprehensively evaluate the early stage of FP and grasp the rules of outcome and evolution of FP by noninvasive and dynamic visualization of objective evaluation indicators, which could help explore the mechanism of acupuncture treatment and make clinical acupuncture treatment for FP more predictable, targeted, and proactive.

In recent years, with the internationalization of acupuncture, more and more evidences have shown^[13,14]^ that acupuncture was scientific in treating and preventing certain diseases. Visualization research has led to qualitative changes in western medicine diagnosis and treatment, so we believe that visualization research may also become a breakthrough path for the technological advancement of Chinese medicine.^[15]^ For example, Laser Speckle Contrast Analysis (LASCA)^[16]^ can use the backward dynamic speckle contrast value generated by red blood cell movement in blood vessels to obtain blood flow velocity information and acquire a 2-dimensional high-resolution blood flow distribution image, which is a good indicator for monitoring superficial microcirculation perfusion of the skin and can be applied to PFP research. Our previous study has demonstrated that the blood flow on the affected side of the patient with FP was lower than that on the healthy side by using the technology of LASCA.^[17,18]^ Furthermore, upper and lower extremity stroke rehabilitation training system based on VR technology can be quickly copied to the FP training rehabilitation system. Here, our aim is to expolre the acupuncture mechanism on FP therapy based on LASCA technology combined with deep learning and image segmentation, which can help patients with FP recovery by developing dynamic interactive FP rehabilitation exercises depended on virtual reality technology.

## Methods

2

### Design

2.1

This study is an observational trial conducted in Shenzhen Hospital of Traditional Chinese Medicine, China. After getting written informed consent, H-B scale, BR, facial structure symmetry analysis, and LASCA technique testing were performed on 200 eligible patients with PFP. The primary objective is to provide a new visual and objective evaluation method for studying the mechanism and efficacy of acupuncture treatment of FP and develop an interactive augmented reality facial nerve function rehabilitation training system with multiple training modes. The study flow chart is showed in Figure 1.

**Figure 1 F1:**
[figure not shown]
Flow chart and technical roadmap of this project.

### Sample collection

2.2

Sample size is calculated based on previous observation research results using PASS.11 software.^[18]^ Two hundred patients with FP who met the requirements were registered and their personal files were established in research database from 2020.5 to 2022.5.

### Diagnostic criteria

2.3

Participants must meet the western medical diagnostic criteria (Table 1, with reference to the fifth edition of the textbook “Neurology” edited by Wang Weizhi), and the traditional Chinese medical (TCM) diagnostic criteria and syndrome differentiation (Tables 2 and 3, with reference to the textbook “Acupuncture and Moxibustion” edited by Shi Xuemin). The judgment of syndrome differentiation will be determined independently by 2 designated deputy physicians of TCM.

**Table 1 T1:** Western medical diagnostic criteria for facial paralysis.

1. Medical history: urgent onset, often with a history of catching a cold or blowing, or a history of viral infection.
2. Main clinical manifestation: sudden paralysis of facial expression muscles on 1 side, disappearance of forehead lines on the sick side, nonclosable eyelids, shallowed nasolabial fold, sagging mouth angle, drum cheek, leak when whistling and food tends to be stayed between the teeth and cheek on the affected side.
3. Accompanying clinical manifestation: loss of taste of the front two-thirds of the tongue on the affected side, hyperacusis, and more tears.
4. Auxiliary examination: normal brain CT and MRI examinations

CT = computed tomography, MRI = magnetic resonance imaging.

**Table 2 T2:** Diagnostic criteria for traditional Chinese medical of facial paralysis.

1. Sudden onset of illness, often with a history of catching a cold, mostly in spring and autumn
2. Facial stagnation, numbness and tears on one side, disappearance of forehead lines, shallowed nasolabial fold, nonclosable eyes, mouth corner pulled toward the healthy side, or pain or fever of the cheek, the ear, or behind the ear on one side.
3. Failed to close eye, drum cheek, or show teeth on 1 side
4. Abnormal EGM

EGM = electromyogram.

**Table 3 T3:** Diagnostic criteria for TCM syndrome differentiation of facial paralysis.

1. Syndrome of wind-cold invading collaterals: sudden appearance of skewed mouth and eyes, incompletely closed eyelids, history of catching cold on the face, pale tongue, thin and white fur, floating and tight pulse.
2. Syndrome of wind-heat invading collaterals: sudden appearance of skewed mouth and eyes, incompletely closed eyelids, secondary to cold and fever, or a history of throat infections, red tongue, yellow and greasy fur, floating and rapid pulse.
3. Syndrome of wind-phlegm obstructing collaterals: sudden appearance of skewed mouth and eyes, incompletely closed eyelids, or facial jerking, numb and swollen face, with heavy head, chest tightness, or spitting, plump tongue, white and greasy fur, stringy and slippery pulse.
4. Syndrome of qi deficiency and blood stasis collaterals: more common in patients with a recovery period or a longer course of disease, tired and weak limbs, pale complexion, dizziness, skewed mouth and eyes, incompletely closed eyelids for a long time, jerking facial muscles, pale and purplish tongue, thin and white fur, thready and hesitant pulse or thready and weak pulse.

TCM = Traditional Chinese Medicine.

### Eligibility criteria and exclusion criteria

2.4

The included patients are in accordance with the following eligibility criteria: participants meet the diagnostic criteria for PFP; participants have their first onset and the course of disease is within 3 months; participants have unilateral facial muscle paralysis; participants are aged between 15 and 70 years; participants offer informed consent and volunteered to participate in the trial.

Participants meet with these exclusion criteria and are excluded: FP of patient is secondary to other diseases, such as Gillan-Barre syndrome, otogenic facial neuritis (such as otitis media, labyrinthitis, mastoiditis, mumps, and so on), posterior cranial fossa tumors, and meningitis; patients with severe primary diseases such as diabetes, cardiovascular and cerebrovascular disease, liver disease, kidney disease, and patients with mental illness; patients with Hunt syndrome; patients who are younger than 15 years or older than 70 years, women that are pregnant or in lactating.

### Acupuncture treatment protocol

2.5

All the patients receive acupuncture treatments 5 times/week for a total of 20 sessions over 4 weeks. In the acupuncture treatment, 14 main acupoints are used (acupoints of Yangbai, Zanzhu, Sizhukong, Sibai, Xiaguan, Yingxiang, Dicang, Jiache, Qianzheng, Yifeng on the affected side, and acupoints of Hegu, Taichong on both sides). Minor points can be added and subtracted according to different syndrome differentiation, physique and symptoms, for example, Lianquan is added when taste sense of the front two-thirds of the tongue is loss.

In addition, there is difference in the operation of acupuncture. Acupuncture operation in the acute phase should be light and shallow, without twisting and lifting, and electroacupuncture is forbidden, whereas mild-reinforcing and mild-reducing method is usually used in acupuncture of the recovery period. Electroacupuncture can be chosen for patients with facial muscle atrophy, two pairs of points including Xiaguan-Juliao and Jiache-Dicang are generally chosen and the time is last for 30 minutes. During the period of electroacupuncture, continuous waves are used, with a frequency of 1 to 2 Hz and the output intensity is based on the slight contraction of facial muscles.

### Surface blood flow signal collection of face

2.6

PeriCam PSI laser speckle imager (Perimed, Sweden) is applied for surface blood flow signal collection of face. The parameter is set as followings: high resolution, 10 images/s of frequency, the acquisition frequency is 50 Hz, and the sampling density is medium. After that, facial blood perfusion volume is recorded over 3 periods: 5 minutes that the patient lies flat and quietly; the whole process of acupuncture; 5 minutes after needle removal. The evaluation criteria for FP in LASCA are shown in Table 4. When monitoring, the patient is in a supine position, facing directly above, and the laser emission and monitoring head are placed about 25 to 30 cm directly above the patient's face.

**Table 4 T4:** Evaluation criteria for facial paralysis in LASCA.

1. ROI: In machine vision and image processing, machine learning and image segmentation methods are used to automatically divide the facial blood flow image into 6 regions: left and right eye area, left and right cheek area, and left and right jaw area.
2. TOI: In machine vision and image processing, periods of interest are selected. Generally, 3 periods are taken: before acupuncture (5 min), during acupuncture (20 min), after acupuncture (5 min).
3. Pr: Pr = P1 (average blood perfusion volume on the healthy side)/P2 (average blood perfusion volume on the affected side). The closer Pr is to 1, the faster the recovery, the better the curative effect, and the better the prognosis.

LASCA = laser speckle contrast analysis.

### Nerve electromyogram signal collection using H-B rating scale

2.7

Viking Quest EMG system (Thermo Nicolet Corporation, America) is utilized for nerve electromyogram (EGM) signal collection, and room temperature is maintained at 18°C to 25°C. When the patient is performed with BR of facial nerve, we choose a repetitive waveform to measure the shortest latency of R1 and R2 (Table 5). After that facial nerve function before and after acupuncture intervention is assessed by using H-B rating scale (Table 6).

**Table 5 T5:** Evaluation criteria for facial paralysis in BR.

1. The latency of R1 is 10.0 ± 0.6 ms, when the latency of R1 is ≥2 ms and the difference between the latency of bilateral R1 is ≥2.0 ms, these data can be judged as abnormal.
2. The latency of R2 is 29.3 ± 1.8 ms, and the latency that ≥34 ms can be judged as abnormal.
3. Undetectable or absent signal of R1, R2, and contralateral R2 ′is considered as abnormal.

BR = blink reflex.

**Table 6 T6:** H-B rating scale.

1. Mild: H-B rating scale has a local score of II
2. Moderate: H-B rating scale has a local score of III-IV
3. Moderate to severe: H-B rating scale has a local score of V
4. Severe: H-B rating scale has a local score of VI

H-B = House-Brakmann.

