### Statistical analysis

2.9

SPSS 20.0 statistical software is used for statistical analysis of data (SPSS Inc, Chicago, IL). The correlation between H-B score, BR, and Pr would be analyzed by correlation analysis, the closer the correlation coefficient is to 1 or −1, the stronger the correlation, the closer the correlation coefficient to 0, the weaker the correlation. Radit analysis is adopted to analyze H-B facial nerve function rating scale. In terms of surface blood perfusion signal analysis, statistical analysis is mainly performed on Pr values before and after treatment. Data are expressed as “mean ± SD” and homologous paired sample t test is utilized. COX regression analysis is used to analyze the development of FP and the prediction on model of its prognosis and outcomes. *P* < .05 indicates that the difference is statistically significant, as well as *P* < .01 means that the statistical significance is remarkable.

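### Table 5 sets the absolute R1 limit at ≥2 ms beside a reference of 10.0 ± 0.6 ms, so that limb has no effect and the R1 rule reduces to the side difference alone

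*Protocol article*

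**What the plan says.** The blink-reflex scoring rule is in the protocol article, section 2.7, Table 5. It has three items.

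- **Item 1 (R1).** The reference is "The latency of R1 is 10.0 ± 0.6 ms". The abnormality rule follows in the same sentence and has two limbs joined by *and*: "when the latency of R1 is ≥2 ms and the difference between the latency of bilateral R1 is ≥2.0 ms".
- **Item 2 (R2).** "The latency of R2 is 29.3 ± 1.8 ms, and the latency that ≥34 ms can be judged as abnormal".
- **Item 3 (no response).** "Undetectable or absent signal of R1, R2, and contralateral R2" counts as abnormal under a rule of its own.

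Section 2.1 lists blink reflex among the tests done on the 200 patients. Section 2.9 then says: "The correlation between H-B score, BR, and Pr would be analyzed by correlation analysis". It does not say whether blink reflex enters as a latency or as normal/abnormal. Nothing else in the article gives another absolute R1 limit or explains the 2 ms.

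**The concern.** A latency limit for abnormality should lie above the reference mean, because the rule is looking for delayed conduction. The R2 limit does. The R1 limit lies far below its mean, in the same sentence that states that mean. An absolute limb met by every recordable response separates no one.

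At stake is the classification of blink-reflex results. Table 5 is the only blink-reflex scoring rule in the article, and the measure is one of those set against the LASCA ratio Pr. As printed, item 1 does not apply the two-part rule that the table appears to intend. Assessors who notice the oddity and silently correct it in different ways could score the same recording differently.

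**Working it through.** **Inputs (all from section 2.7, Table 5).** R1 reference 10.0 ± 0.6 ms; R1 limbs: latency ≥2 ms and bilateral difference ≥2.0 ms; R2 reference 29.3 ± 1.8 ms; R2 limit ≥34 ms. Assumptions: the printed latencies are reference values in normals, ± is a standard deviation, and latencies are roughly normally distributed.

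**1. Position of each limit.** z = (limit − mean) / SD.

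| Limit | Calculation | z | Share of normals at or above |
|---|---|---|---|
| R1 ≥2 ms | (2 − 10.0) / 0.6 | −13.3 | 1.000 |
| R2 ≥34 ms | (34 − 29.3) / 1.8 | +2.61 | 0.0045 (0.45%) |

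The R1 result does not hang on how ± is read. With an SD of 3 ms, five times the printed figure, the share of normals at or above 2 ms is still 0.996.

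**2. Can the 2 ms be reproduced as an upper-tail limit?**

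- Mean + 2 SD: 10.0 + 2 × 0.6 = 11.2 ms
- Mean + 2.61 SD (the position of the R2 limit): 10.0 + 2.61 × 0.6 ≈ 11.6 ms
- Mean + 3 SD: 10.0 + 3 × 0.6 = 11.8 ms

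None gives 2 ms. These figures are a consistency check and not proposed limits.

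**3. Does the absolute limb ever change the joint rule?** Let the latency limb apply to the longer side. If the two sides differ by at least 2.0 ms and the shorter latency is not negative, the longer latency is at least 0 + 2.0 = 2.0 ms. The second limb therefore implies the first. A grid of both sides from 0 to 40 ms in 0.1 ms steps agrees: the joint rule and the side-difference rule alone gave 0 discordant pairs.

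**4. Does the remaining limb discriminate?** The SD of the side difference in normals is 0.6 × √(2(1 − ρ)), where ρ is the between-side correlation. The article does not give ρ, so a range is shown.

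| Assumed ρ | SD of difference (ms) | 2.0 ms in SDs | Normals flagged (two-sided) |
|---|---|---|---|
| 0 | 0.85 | 2.36 | 1.8% |
| 0.3 | 0.71 | 2.82 | 0.48% |
| 0.5 | 0.60 | 3.33 | 0.09% |

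So the rule that remains is a usable test of asymmetry. It does not register absolute prolongation: if both sides read 14 ms, for illustration, the difference is 0 and item 1 does not flag R1.

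**The case against.** The strongest reply is that the printed rule still works. With *and* between the limbs, the idle limb adds no false positives, and the side difference flags few normals. R2 and absent responses have usable rules of their own. The figure may simply be a slip: a lost digit, a repeat of the 2.0 ms criterion, or an excess over the reference value. On that last reading the limb would not be idle. All of this stands, and it limits the consequence. It does not remove the error, because the sentence as printed contradicts its own reference and the article does not say which reading applies.

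Three stronger readings are tempting and are not supported.

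- **A reader might infer that every nerve is called abnormal.** That would need the 2 ms limb to act alone or the limbs to be joined by *or*. Table 5 says *and*.
- **A reader might infer that the comparison of Pr with blink reflex and H-B is spoiled.** Section 2.7 records R1 and R2 latencies, and section 2.9 does not say that blink reflex is dichotomised. If it enters as a continuous latency, the limit has little bearing on the result. Nor does the validation of LASCA rest on blink reflex and H-B alone, since the abstract and section 2.1 also include facial structure symmetry.
- **A reader might want section 2.9 rebuilt around the continuous affected-minus-healthy R1 difference.** Patients with an absent R1 have no such difference, although item 3 counts them as abnormal. They would drop out unless a further rule were added.

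**Conclusion.** The point holds as an error in a stated decision threshold. The absolute R1 limb is 13.3 SD on the wrong side of its own reference mean (with ± as SD), every detectable R1 meets it, and it never changes a classification. The effective R1 rule is a bilateral difference of at least 2.0 ms. Under the assumed correlations of 0 to 0.5, that rule flags between 1.8% and 0.09% of normals.

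The loss is confined to the absolute criterion: item 1 does not flag an R1 that is prolonged but differs by less than 2.0 ms between sides. How far this reaches the results depends on something section 2.9 does not state. It matters wherever blink reflex is scored normal/abnormal through item 1, and it is small if only continuous latencies are correlated. That 2 ms is not an upper-tail limit for R1 follows from the table alone. What figure or wording was meant cannot be settled from the article.

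**What to change.** Before any blink-reflex recording is classified, the investigators should correct Table 5 item 1 in one of three ways, according to what was meant:

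- reconcile the absolute R1 figure with the table's own reference range and with the source of that range;
- delete the limb, if the 2 ms merely repeats the side-difference criterion;
- say so explicitly, if the 2 ms means an excess over the reference value.

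They should then confirm that *and* is still intended, because once the absolute limb has an effect the choice of connective changes who is flagged. No particular limit is proposed here, and section 2.9 does not need to be redesigned on this account.

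The cost is one figure or phrase in Table 5 and a sentence confirming the connective. No extra measurements are needed. Any recordings already scored under item 1 could be rescored if their R1 latencies were kept.

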### Adverse events and other unintended effects

2.8

We will collect, assess, report, and manage solicited and spontaneously reported adverse events and other unintended effects of trial interventions or trial conduct, with which we could evaluate the safety of acupuncture treatment.

### Statistical analysis

2.9

SPSS 20.0 statistical software is used for statistical analysis of data (SPSS Inc, Chicago, IL). The correlation between H-B score, BR, and Pr would be analyzed by correlation analysis, the closer the correlation coefficient is to 1 or −1, the stronger the correlation, the closer the correlation coefficient to 0, the weaker the correlation. Radit analysis is adopted to analyze H-B facial nerve function rating scale. In terms of surface blood perfusion signal analysis, statistical analysis is mainly performed on Pr values before and after treatment. Data are expressed as “mean ± SD” and homologous paired sample t test is utilized. COX regression analysis is used to analyze the development of FP and the prediction on model of its prognosis and outcomes. *P* < .05 indicates that the difference is statistically significant, as well as *P* < .01 means that the statistical significance is remarkable.

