**Methods::**

This prospective and observational trial will recruit 200 eligible participants for the following study. In the trial, the laser speckle contrast analysis (LASCA) technology will be applied to monitor the microcirculation of facial blood flow during acupuncture, and real-time monitoring algorithms, data sampling, and digital imaging methods will be conducted by machine learning and image segmentation. Then, a database of patient facial expressions will be built, the correlation between surface blood flow perfusion volume and facial structure symmetry will be analyzed, combined with scale assessment and electrophysiological detection. In addition, we will also explore the objectivity and effectiveness of LASCA in the evaluation of facial paralysis (FP), and the changes in blood flow microcirculation before and after acupuncture treatment will be analyzed.

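### The before-after blood-flow test named in section 2.9 is on the healthy/affected ratio Pr only, and Pr alone cannot show whether affected-side flow changed

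*Protocol article*

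**What the plan says.** All references are to the protocol article.

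- **Aim.** The Abstract (Methods) promises that "the changes in blood flow microcirculation before and after acupuncture treatment will be analyzed".
- **Measure.** Section 2.6, Table 4 item 3, defines "Pr = P1 (average blood perfusion volume on the healthy side)/P2 (average blood perfusion volume on the affected side"), and gives a reading rule: "The closer Pr is to 1, the faster the recovery, the better the curative effect, and the better the prognosis". The rule does not depend on which side moved.
- **Analysis.** Section 2.9 states that "statistical analysis is mainly performed on Pr values before and after treatment", and that a "homologous paired sample t test is utilized". It names no before-after test of P1 or P2 alone.
- **Expected starting point.** The Introduction reports from the group's own earlier work that "the blood flow on the affected side of the patient with FP was lower than that on the healthy side". Pr should therefore start above 1.
- **Treatment.** Section 2.5 lists 14 main points. Ten are on the affected side. The rest are the "acupoints of Hegu, Taichong on both sides".
- **Data.** Table 4 item 1 divides the face into separate left and right areas, so P1 and P2 both exist before Pr is formed. The Abstract (Results) says the two sides will be compared. That is a comparison between sides, not a change over time on each side.

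**The concern.** The aim concerns flow, and the Introduction's rationale is that the nerve recovers when its blood supply is good. The quantity tested is the balance between two flows. A ratio discards the level of both sides and does not show which side moved.

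Two misreadings become possible. A microcirculatory response of similar relative size on both sides would appear as no change. Such a response is not far-fetched, because part of the needling is bilateral. Conversely, a fall in healthy-side flow would bring Pr towards 1, and Table 4 would count it as better curative effect although the affected side had gained nothing. Because the reading rule is written into the plan, a report that follows it could draw either conclusion without departing from the protocol.

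**Working it through.** The article gives 200 patients but no SD, effect size or power for Pr, so there is no stated figure to reproduce. The check is algebra on the protocol's own definition, then illustrative numbers.

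**1. What Pr responds to.** Since Pr = P1/P2, ln Pr = ln P1 − ln P2. The before-after change is therefore

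Δ ln Pr = Δ ln P1 − Δ ln P2.

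If both sides change by the same factor, the right-hand side is zero. A given fall in Pr fixes only the difference of the two terms and not either one.

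**2. Illustrative values.** Take P1 = 100 (healthy) and P2 = 80 (affected). These are assumed; only their order comes from the Introduction. Baseline Pr = 100/80 = 1.25.

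| Change | P1 / P2 after | Pr after | Table 4 reading | Affected side |
|---|---|---|---|---|
| Both +30% | 130 / 104 | 1.25 | no change | +30% |
| Both −30% | 70 / 56 | 1.25 | no change | −30% |
| Affected side rises only | 100 / 100 | 1.00 | better | +25% |
| Healthy side falls only | 80 / 80 | 1.00 | better | 0% |
| Both fall, healthy more | 72 / 64 | 1.125 | better | −20% |
| Both rise, healthy more | 140 / 100 | 1.40 | worse | +25% |
| Both +20 units | 120 / 100 | 1.20 | better | +25% |

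Rows 1 and 2 are opposite effects with the same Pr, and so are indistinguishable. Rows 3 and 4 also share one Pr. The last row marks the limit of the point: a two-sided change that is not proportional does move Pr.

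**3. Is a two-sided response conceivable?** Section 2.5 gives 10 affected-side points and 2 × 2 = 4 bilateral ones, 14 in total. So 4 of the 14 main points are bilateral pairs.

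**4. Rejection rates, for illustration only.** Simulated paired t tests used n = 200, two-sided 5% level and 1000 runs per scenario. Assumptions: log-normal perfusion, affected/healthy ratio 0.8, between-patient log SD 0.25, within-patient log SD 0.1, 0.2 or 0.3.

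| Scenario | Pr test | ln P2 test | ln P1 test |
|---|---|---|---|
| Both sides +20% | 4–5% | about 100% | about 100% |
| Healthy side −10% only | 67–100% | 4–5% | 95–100% |
| Affected side +10% only | 57–100% | 90–100% | about 5% |

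The patient component was held constant between the two recordings, so no session-wide shift was simulated. This flatters the per-side tests, as step 5 shows.

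**5. The price of per-side tests.** Suppose instead that a patient's two sides share a log-change with SD 0.25 between recordings, and each side adds its own change with SD 0.10 (both assumed).

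- Variance of Δ ln P2 = 0.25² + 0.10² = 0.0725, so SD = 0.269.
- Variance of Δ ln Pr = 2 × 0.10² = 0.02, so SD = 0.141.
- For an effect on the affected side only, the P2 test needs 0.0725/0.02 ≈ 3.6 times as many patients as the Pr test.

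In general Pr is the more precise measure of such an effect whenever the shared SD exceeds the side-specific SD. Under these values, 200 patients still give an approximate 95% CI half-width for Δ ln P2 of 1.96 × 0.269/√200 = 0.037, about 4%.

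**The case against.** The strongest defence is that Pr is a sensible main measure. Section 2.4 requires unilateral paralysis, most main points are on the affected side, and there is no control group, so the healthy side is the only within-patient reference. Insensitivity to a shift common to both sides is the purpose of a side contrast. It removes session effects and the effect of a camera placed anywhere from 25 to 30 cm away. A single-arm test of P2 would report any systematic drift as an effect, and step 5 shows that it can be much less precise. All of this stands. It argues for keeping Pr in first place and against making a rise in P2 the sole criterion.

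A second defence is that section 2.9 says *mainly*, and that a condensed article may leave per-side summaries to a fuller document. That is fair as far as it goes, and the absence of detail is not the complaint. The article does, however, state both the test and the reading rule, and that pairing can mislead whatever else is reported.

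A reader might infer more than the text supports:

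- **That Pr hides any two-sided change.** This is exact only for equal percentage changes. Unequal ones move Pr but leave the side unidentified.
- **That healthy-side falls will be passed off as affected-side recovery.** Nothing in the article suggests that treatment lowers healthy-side flow, so the scenario is hypothetical and applies only while Pr is above 1. Table 4 speaks of recovery and curative effect; it does not say that P2 rose.
- **That the simulated percentages forecast this study.** They depend on assumed SDs.

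**Conclusion.** The point holds in a limited form. Section 2.9 names a before-after test only on Pr, and Table 4 interprets any approach to 1 as benefit. By the protocol's own definition Pr is blind to a proportional change on both sides. When it starts above 1, it cannot attribute a fall in Pr to the affected rather than the healthy side. Pr alone therefore answers a question about symmetry and not the stated one about change in microcirculation.

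This conclusion is algebraic and needs no assumed variance. It applies whether the comparison is within a session or across the treatment course. What does rest on assumptions is how often the problem would matter in practice: the perfusion values and SDs used above are illustrative, and the article gives none. The choice of Pr as the main symmetry measure is not an error. The plan should be amended, because the remedy is cheap and uses values already recorded.

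**What to change.** In section 2.9:

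1. Keep Pr as the main symmetry measure, preferably analysed as ln Pr, so that the three results satisfy the identity in step 1 exactly.
2. Beside it, report the before-after change with 95% CI, from a paired analysis on the log scale, for P2 (affected) and P1 (healthy) separately.
3. State that a change in Pr will be described as improved affected-side flow only when the P2 result supports it, and otherwise as a change in symmetry. Qualify the reading rule in Table 4 item 3 to match.
4. In section 2.6, hold the camera distance the same for each patient's repeat recordings.

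**Cost.** The change is wording plus two more reported results; P1 and P2 are already needed to form Pr. The per-side values do not cancel session-to-session shifts or distance effects as Pr does, and fixing the distance removes only one source of drift. They should be labelled supportive.
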